## 2. General Statements

“Monteplase (recombinant)” is a glycoprotein produced from a modified human tPA-derived gene in which the cysteine at the 84th amino-acid residue of the N-terminal region of human tissue-type plasminogen activator (tPA) is replaced by serine; it dissolves thrombi by activating plasminogen in the clot to plasmin. In Japan, intravenous administration for dissolution of coronary-artery thrombi in acute myocardial infarction and pulmonary-artery thrombi in acute pulmonary embolism has already been approved; however, we are now attempting to develop an ophthalmic formulation intended to dissolve thrombi in submacular hemorrhage (SMH).

### 2.1. Purpose of the Study

To evaluate the efficacy and safety of sub-retinal administration of Monteplase (recombinant) for submacular hemorrhage that causes severe visual-function impairment.

### 2.2. Background

SMH is characterized by accumulation of blood beneath the retina, arising from progression of age-related macular degeneration (AMD) or rupture of retinal arterial microaneurysms (RAM). SMH induces retinal damage primarily through toxic, tractional, and barrier effects. The toxic effect is attributable to several substances; a representative example is iron toxicity from erythrocyte-derived ferritin, which damages the choroidal-retinal circulation, photoreceptors, and the retinal pigment epithelium (RPE). The tractional effect results from fibrin generated by the SMH, causing photoreceptor traction and degeneration. The barrier effect interferes with the movement of nutrients and metabolites between the choroid and the outer retinal layers due to the physical presence of SMH. SMH causes acute and severe visual impairment, and in the natural course, over 80 % of patients end with a final visual acuity of less than 0.1. The incidence of SMH with optic-disc diameter  $\geq 2$  disc diameters is reported as 5.4–25 cases per 1,000,000 persons per year, meeting the definition of a rare disease.

Seventy to ninety percent of SMH cases are caused by AMD, and 5–30 % by RAM. In a 10-year observational study of patients with exudative AMD receiving vascular endothelial growth

factor (VEGF) inhibitors, the annual incidence of SMH associated with visual loss was estimated at 0.46 %. AMD is a leading cause of blindness in developed countries, and in Japan, macular degeneration including AMD ranks fourth among causes of visual disability. The prevalence of AMD is estimated at 8.7 % of the world population; because aging is the primary risk factor, a substantial increase in patients is projected worldwide, especially in Asia, during the era of global aging. In a large cohort study in Japan covering the entire population aged  $\geq 40$  years (approximately 76 million), about 246 000 active exudative AMD patients were identified between 2011 and 2018, and prevalence has steadily increased across almost all age groups  $\geq 65$  years. In Japan, the proportion of exudative AMD patients is higher than in Europe and the United States; consequently, the number of SMH cases are expected to rise with the increasing patient population. RAM occurs in the elderly, is more common in women, and is strongly associated with hypertension and arteriosclerosis. The visual prognosis of RAM depends on macular pathology and may be complicated by intra-retinal hemorrhage or secondary macular holes; consequently, eyes with SMH in Japan are generally reported to have poor visual outcomes.

When SMH becomes chronic, it induces irreversible neuro-retinal degeneration that adversely affects visual prognosis, therefore, the therapeutic goal for SMH is to remove the hemorrhage from the macular region, or at least from the fovea, as promptly as possible. The clinical characteristics of SMH—including cause, location, volume, and duration—are heterogeneous, and a definitive treatment guideline has not yet been established. Current management is selected according to the underlying disease and the state of the hemorrhage and includes administration of VEGF-inhibitors aimed at reducing leakage from choroidal neovascularization, intravitreal injection of expansile gas to facilitate hemorrhage displacement, sub-retinal hemorrhage evacuation, retinal photocoagulation, and other disease-specific interventions. tPA is an enzyme involved in the fibrinolytic system; it forms a complex with fibrin and activates plasminogen to plasmin, thereby degrading fibrin and exerting thrombolytic activity. In the early phase of SMH, fibrin induces rupture of the photoreceptor inner and outer segments, and with time leads to destruction of the full retinal thickness. However, Lim et al. reported in 1995 that SMH containing tPA did not form fibrin strands and did not cause photoreceptor rupture. In 1996, Herriot et al. reported treatment of SMH with tPA combined with gas injection. Intravitreal or sub-retinal administration of tPA is thought to reduce fibrin-mediated damage to photoreceptors and the retinal pigment epithelium; when combined with vitrectomy or intravitreal gas, it may promote removal of the lysed clot and thereby mitigate visual loss. Ocular local tPA therapy may be performed with or without concomitant VEGF-inhibitor, via intravitreal injection, or as sub-retinal injection in conjunction with vitrectomy. A review of multiple studies summarizing visual-acuity changes before and after

ocular tPA therapy indicated that the greatest visual improvement was observed with the combination of vitrectomy, sub-retinal tPA injection, intravitreal gas injection, and VEGF-inhibitor therapy.

As of January 2025, tPA is being used off-label worldwide for SMH. In Europe, a randomized prospective trial (the TIGER study: “Vitrectomy, subretinal Tissue plasminogen activator and Intravitreal Gas for submacular hemorrhage secondary to Exudative Age-Related macular degeneration”, a phase 3, pan-European, two-group, non-commercial, active-control, observer-masked, superiority, randomized controlled surgical trial) is underway to evaluate VEGF-inhibitor monotherapy versus surgical therapy (vitrectomy, sub-retinal tPA injection, intravitreal gas injection, and VEGF-inhibitor administration). The alteplase (Actilyse®) used in that trial has not received marketing authorization in Japan.

In Japan, several reports have described the efficacy and safety of ocular local tPA therapy for SMH secondary to AMD or RAM. Nevertheless, tPA remains unapproved for SMH, and off-label use continues in clinical practice. Off-label use is governed by the “Standards for the Use of Unapproved New Drugs, etc., as Determined by the Minister of Health, Labour and Welfare under Article 9-23, Paragraph 1, Item 8-ro of the Medical Care Act Enforcement Ordinance” (Notification from the Director of the Medical Affairs Division, Ministry of Health, Labour and Welfare, 10 June 2016). Accordingly, each institution’s Unapproved New Drug Evaluation Committee conducts an ethical review and determines the appropriateness of use. When use is approved, all treated cases must be reported regularly. Consequently, only a limited number of facilities are able to administer tPA, and no alternative hemolytic agent to tPA is available for displacing sub-macular hemorrhage. Physical constraints—such as difficulty travelling to distant centers due to visual impairment—lead to treatment delays or abandonment for many patients. Therefore, the investigators aim to expand the indication for tPA in the severe ophthalmic condition of SMH, or to develop an ophthalmic formulation, by planning a phase II physician-initiated clinical trial to evaluate the efficacy and safety of sub-retinal tPA administration.

### 2.3. Benefit–Risk Assessment

More detailed information on the known and anticipated benefits and risks of Montepulse (recombinant) and on the reasonably foreseeable adverse events (AE) will be provided in the investigational product dossier for this clinical trial.

#### 2.3.1. Risk Assessment

Adverse events that may occur with administration of monteplase (genetically engineered) include retinal toxicity (retinal morphological changes, etc.), increased sub-macular

hemorrhage, macular hole, vitreous hemorrhage, anterior chamber hemorrhage, endophthalmitis, elevated intra-ocular pressure, retinal detachment, corneal opacity, progression of cataract, etc. In addition to pharmacologic effects of the drug itself, events associated with vitreous surgery or intra-ocular tamponade are also encompassed.

To minimize these risks, the trial sites for this study shall be facilities that have prior experience with sub-retinal administration of tPA preparations, and patients at high risk will be excluded by the exclusion criteria.

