#### 8.4.7. Disease-Related Events

Events that may occur in association with the underlying disease or the surgical procedure include pre-retinal hemorrhage, intraretinal hemorrhage, sub-retinal hemorrhage, vitreous hemorrhage, serous retinal detachment, macular edema, re-bleeding, hard exudates, etc. These

events shall be evaluated, in light of the subject's underlying disease condition, for the anticipated intensity, frequency, duration, and any reasonable possibility of association with the trial intervention, to determine their relevance as an AE or SAE and to assess causality with the investigational product.

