#### 9.6. Safety Analyses

For the following items, the number of subjects evaluated, the number of events, and the incidence proportion will be calculated.

- Adverse events, adverse drug reactions
- Serious adverse events, serious adverse drug reactions
- Adverse events resulting in death, adverse drug reactions resulting in death
- Adverse events leading to discontinuation of the trial, adverse drug reactions leading to discontinuation of the trial

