##### [Items]

- Adverse event name
- Onset date
- Severity classification (mild / moderate / severe)
- Seriousness classification (serious / non-serious)
- Causality assessment (no relationship / relationship present)
- Outcome (recovered / improved / not recovered (unchanged) / recovered with sequelae / death / unknown)
- Outcome date
- Management (whether treatment was given and its details)

The principal investigator or sub-investigator shall, based on signs, symptoms, and/or other clinical information, make every effort to identify the diagnostic term for the event. When possible, the diagnostic term—not individual signs or symptoms—should be recorded as an AE/SAE.

<Severity Assessment>

The principal investigator or sub-investigator shall classify the severity of an adverse event according to the following definitions:

Mild: Discomfort is present but does not interfere with daily activities.

Moderate: Some interference with daily activities is observed.

Severe: The subject is unable to carry out daily activities or work.

<Causality Assessment>

The principal investigator or sub-investigator shall evaluate the relationship between the investigational product and each AE/SAE and determine clinically whether a causal relationship is “present” or “absent.”

Causality determinations shall be made as follows:

✓ No relationship

The event can be clearly explained by comorbidities, medical history, concomitant medications, the known pharmacologic properties of the investigational product, or other known causes such as surgery.

✓ Relationship present (all three criteria must be satisfied)

- i. The temporal relationship between the onset of the event and the administration of the investigational product can be reasonably explained.
- ii. The event could plausibly arise from the pharmacologic action, physicochemical properties, route of administration, or other known characteristics of the investigational product or similar agents, or the principal investigator/sub-investigator acknowledges a causal relationship.
- iii. The subject’s comorbidities, medical history, concomitant drugs, or concomitant therapies are not considered contributory.

In performing the causality assessment, the principal investigator or sub-investigator shall refer to the Investigator’s Brochure, the product label, and the interview form.

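### The causality rule in Section 10.2.3 lets a harm of the sub-retinal injection be coded as related or unrelated, and no adverse event item records relation to the trial procedure

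*Protocol*

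**What the plan says.** All references are to the protocol.

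- **Objective (Section 3).** The safety objective concerns sub-retinal administration of monteplase, and its endpoint is adverse events.
- **Risk description (Section 2.3.1).** After listing events that may follow administration, the section adds that, beyond the drug's own pharmacology, "events associated with vitreous surgery or intra-ocular tamponade are also encompassed".
- **What is judged (Section 10.2.3).** The investigator "shall evaluate the relationship between the investigational product and each AE/SAE". The recorded item is "Causality assessment (no relationship / relationship present", a single binary field. None of the other listed items concerns relation to the vitrectomy, the injection or the tamponade.
- **Ground for unrelated (Section 10.2.3).** The event is clearly explained by one of several causes, ending "or other known causes such as surgery". No exception is made for the trial's own Day 1 operation.
- **Grounds for related (Section 10.2.3).** Three criteria must all hold. Criterion ii is met if, among other things, the event could arise from the "route of administration, or other known characteristics of the investigational product or similar agents".
- **Disease- and surgery-related events (Section 8.4.7).** The investigator weighs "any reasonable possibility of association with the trial intervention", and the same sentence ends by asking for causality with the investigational product.
- **Tables (Section 9.6).** The first entry is "Adverse events, adverse drug reactions". The same pairing of all events with drug reactions follows for serious events, deaths and events leading to discontinuation.

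**The concern.** Monteplase reaches the sub-retinal space only through an operation. Under Tables 6-1 and 6-2, every subject has vitrectomy, a sub-retinal injection and a gas or oil tamponade in one session. A causality rule that treats surgery as an alternative explanation therefore has to say which part of that session counts as surgery and which counts as giving the drug. Section 10.2.3 does not.

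The case is not remote. Section 4.2 rejects a placebo arm partly because a sub-retinal placebo injection could itself detach the retina. The protocol thus accepts that the injection can do harm without the drug, but gives no rule for coding such a harm.

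What is at stake is the meaning of the related-event counts. The trial is multicentre, unblinded and single-arm, and Section 10.1.9 sets up no committee. There is no control rate for comparison, and the protocol describes no central adjudication that would make coding uniform. If two investigators read the rule differently, the adverse drug reaction rows mix two definitions. Procedural harm can then be found only by going through the all-cause list and judging each event afterwards.

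**Working it through.** The protocol states no figure on this point. The check is to apply Section 10.2.3 to each source of harm in turn.

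**1. Harm clearly explained by vitrectomy or tamponade.** The surgery ground applies and the event is coded unrelated. It is absent from all four drug-reaction counts in Section 9.6 and present in the all-cause counts. That agrees with Section 10.2.1, which defines a side effect by its causal link to the product. The gap is that no listed item records that the trial procedure caused it.

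**2. Harm of the sub-retinal injection.** Two routes are open.

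| Step in Section 10.2.3 | Reading A | Reading B |
|---|---|---|
| Is the injection surgery? | Yes: it is a step of the operation in Table 6-2 | No: Table 6-1 gives it as the product's route of administration |
| Clause that applies | Other known cause (surgery) | Criterion ii (route of administration) |
| Criterion iii | Not reached | Surgery is not named as an excluding factor |
| Code | Unrelated | Related, if timing fits |

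Both readings follow the text, and nothing in the section ranks one clause above the other.

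**3. Is the answer recorded elsewhere?** Section 8.4.7 asks about the trial intervention, and Section 8.4.1 mentions relation to trial participation for late serious events. Neither has a matching field among the adverse event items in Section 10.2.3.

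**4. Size.** Assume the full target of 20 subjects (Section 9.9) is treated. One subject coded the other way changes the related incidence by 1/20 = 5 percentage points.

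As an illustration with an assumed count, let two subjects have an injection harm and no other related event. The limits are exact (Clopper-Pearson) 95% limits.

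| Coding of the two subjects | Related incidence | 95% limits |
|---|---|---|
| Both by Reading A | 0/20 = 0% | 0 to 1 − 0.025^(1/20) = 16.8% |
| One each way | 1/20 = 5% | 0.1% to 24.9% |
| Both by Reading B | 2/20 = 10% | 1.2% to 31.7% |

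The same clinical facts can give any of these three rows. The all-cause incidence of the injection harm is 2/20 in each. The count of two is not a forecast; the protocol gives no expected rate.

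**The case against.** The strongest reply has four parts.

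- **The drug is the thing under test.** Table 6-1 labels monteplase the investigational product and vitrectomy adjunctive surgery. Coding a vitrectomy complication as not a drug reaction is what the side-effect definition intends. Section 2.3.1 describes foreseeable risks; it is not a coding rule, and it separates pharmacology from surgery. This stands. A reader might infer that Sections 2.3.1 and 10.2.3 contradict each other, but the conflict lies inside Section 10.2.3.
- **Criterion ii already protects injection harms.** A reader might infer that the surgery clause removes every injection harm from the reaction tables. The text does not support that: route of administration is an accepted ground, criterion iii does not name surgery, and the unrelated code needs a clear alternative explanation. What remains is ambiguity, not certain exclusion.
- **No event is lost.** The safety endpoint is adverse events, and each is recorded with name, onset, severity, seriousness and outcome. With 20 subjects, a retinal detachment can be found by name. This stands too, but identifying an event is different from having the treating investigator's judgement of its cause.
- **Other documents may cover it.** Table layout can be left to a statistical analysis plan, and serious events are also handled under a separate safety procedure. However, an analysis plan can only tabulate what was collected, and the item list and causality rule are set in the protocol.

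A separate oddity in the same sentence should not be confused with this point. The grounds for unrelated include "the known pharmacologic properties of the investigational product, or other known causes such as surgery", so the drug's own pharmacology counts against relatedness there and for it in criterion ii. Correcting that wording would leave the present ambiguity in place.

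**Conclusion.** The point holds as a matter of ambiguous coding and an unrecorded judgement. Section 10.2.3 allows opposite codes for a harm of the sub-retinal injection. Harms of the vitrectomy and tamponade are coded unrelated, with no record of their procedural origin. The drug-reaction rows of Section 9.6 may therefore be inconsistent between investigators, by 5 percentage points of incidence per affected subject if 20 are treated.

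The documents do not show that harms vanish from the safety report, or that any particular number of events will be miscoded. Section 2.3.1 names ten events but does not assign a cause to each, so no share of them can be called procedural from the text alone.

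The conclusion assumes that the case report form follows the item list in Section 10.2.3 and that no separate procedure resolves the ambiguity; neither document is shown. The primary efficacy analysis is untouched. This is a cheap improvement that serves the stated safety objective.

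**What to change.** 1. In Section 10.2.3, record two causality judgements for each adverse event: (a) monteplase, including its sub-retinal injection as the route of administration; and (b) the trial procedure, meaning vitrectomy, injection, and gas or oil tamponade.
2. Keep surgery as a ground for unrelated under (a), but state that it does not cover the sub-retinal injection itself. Barring all trial surgery as a ground would be a mistake, because a harm plainly due to the vitrectomy could then no longer be called unrelated to monteplase on that basis.
3. In Section 9.6, beside the drug-reaction rows, add the number and proportion of adverse events and serious adverse events related to the procedure, and related to either.
4. If subjects have already been treated when the change takes effect, ask for both judgements on their events as well, so that one definition runs through the trial.

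The cost is a protocol wording change, one extra case report form item per adverse event and a few table rows. The reported count of related events will look less favourable.

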### 2.3.2. Benefit Assessment

Subjects are expected to benefit from sub-retinal administration of monteplase (genetically engineered) through promotion of hematoma displacement and absorption, leading to improvement in visual prognosis. Furthermore, patients who currently cannot receive sub-retinal monteplase (genetically engineered) because of off-label use and geographic constraints may obtain treatment by participating in this decentralized clinical trial.

### 2.3.3. Conclusion on Benefit–Risk Balance

Considering the measures taken to minimize risk for subjects participating in this trial, the potential risks identified in relation to the investigational intervention and study procedures are justified by the anticipated benefits to subjects with sub-macular hemorrhage.

## 3. Study Objectives, Endpoints and Estimand

| Objective                                                                                                                                                          | Endpoints                                                                                                                                                                                                                                                                         |
|--------------------------------------------------------------------------------------------------------------------------------------------------------------------|-----------------------------------------------------------------------------------------------------------------------------------------------------------------------------------------------------------------------------------------------------------------------------------|
| Primary                                                                                                                                                            |                                                                                                                                                                                                                                                                                   |
| To evaluate the efficacy of sub-retinal Monteplase (recombinant) on central macular hemorrhage in patients with SMH secondary to AMD or RAM.                       | Change in central foveal thickness(CFT) from baseline at Week 1.                                                                                                                                                                                                                  |
| Secondary (Efficacy)                                                                                                                                               |                                                                                                                                                                                                                                                                                   |
| Evaluation of the efficacy of sub-retinal Monteplase (recombinant) in patients with SMH secondary to AMD or RAM, using ophthalmic examination findings as indices. | <Efficacy Evaluation Items>
1) Change in CFT from baseline at Week 4.
2) Presence or absence of a foveal hemorrhage measuring $\geq 1$ disc diameter at Week 4.
3) BCVA (logMAR equivalent) at Week 4.
4) Change in BCVA (logMAR equivalent) from baseline at Week 4. |

|                                                                                                        |                                                                                                                                                          |
|--------------------------------------------------------------------------------------------------------|----------------------------------------------------------------------------------------------------------------------------------------------------------|
|                                                                                                        | 5) Change in CFT from baseline at Week 12.
6) BCVA (logMAR equivalent) at Week 12.
7) Change in BCVA (logMAR equivalent) from baseline at Week 12. |
| Secondary (safety)                                                                                     |                                                                                                                                                          |
| To evaluate the safety of subretinal administration of montepilase (recombinant) in patients with SMH. | Adverse events                                                                                                                                           |

